#### 11.3.1 Interim analysis and early termination

We will perform one interim analysis one year (+/- 2 months) after the inclusion of the first patient. If group comparison between the decolonization and non-decolonization arms are striking and statistically significant in terms of any study objectives, the independent Data Monitoring committee will decide upon the interruption and early termination of the trial. Otherwise, the study continues. Of note, the Data Monitoring committee has the right to call on a premature, additional interim analysis.

If the crude group comparison analysis is not sufficiently meaningful, we will perform a futility analysis to check if the expected statistical power for the final analysis will not be  $< 30\%$  and therefore unacceptable. If it is lower than  $30\%$ , we will consider the trial will not be able to demonstrate the result, and the recruitment will be no more ethical. The most frequent conditional power evaluated under the current trend (i.e. using the information from the collected data) will be assessed. It was demonstrated that futility analyses decrease the statistical power of the final analysis in superiority trials, but in our knowledge, this topic was not explored for non-inferiority trials. To balance (at least partially) this loss of power, we may recruit 100 supplementary patients per arm. E.g. approximately 600 episodes in each randomization arm.

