### 1.6 Data Safety Monitoring Committee

A data safety committee of two persons with experience in clinical research and biostatistics who are not part of the investigators or future authors of the scientific publication will monitor the safety of data and of the study; during the interim analyses (approximatively after one and two years into the study).

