## 5. STUDY OUTCOMES

### Primary outcomes:

- Remission (and inversely superficial or deep-space SSI and revision surgeries for non-infected wound problems; composite primary outcome) at 6 weeks (and/or a 1 year for surgeries with implant)

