### 11.4 Handling of missing data and drop-outs

Missing data regarding the outcome parameters and the decolonization will lead to patient dropout of the study. Drop-outs will be reported in the patients & methods section of the publication, drop-out of data will be reported for a minimum of 10 years after study termination or in case of premature termination of the clinical trial. Major deviations from the protocol will be regarded as drop-outs and excluded from both, the ITT and the PP populations. The independent Data Monitoring Committee may help in case of difficult interpretations of the case among the trial investigators.

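### The calendar-timed interim falls before the 1-year implant outcome can mature, and a crude count of pending implant episodes misstates the event rates and can decide the futility rule

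*Protocol*

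**What the plan says.** Section 11.3.1 of the protocol places the planned interim at a calendar date: "We will perform one interim analysis one year (+/- 2 months) after the inclusion of the first patient". The monitoring committee decides on early termination if the arms' results "are striking and statistically significant in terms of any study objectives". Otherwise the text continues: "If the crude group comparison analysis is not sufficiently meaningful, we will perform a futility analysis". Recruitment is regarded as no longer ethical if expected power is below 30%, and the measure is described so: "The most frequent conditional power evaluated under the current trend (i.e. using the information from the collected data) will be assessed".

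The primary outcome in section 5 is a "composite primary outcome) at 6 weeks (and/or a 1 year for surgeries with implant". Section 3.2.1 allows remission with retained implants to be declared only after at least one year. Section 9.2 gives the implant follow-up contact a window of 2 months either side of 1 year, so month 10 is the earliest.

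Three other sections bear on how an unfinished episode is counted:

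- Section 11.4: "Missing data regarding the outcome parameters and the decolonization will lead to patient dropout of the study".
- Section 11.3.2 defines the per-protocol set as those who complete the study or are classed as failures.
- Section 11.3 names chi-square and exact tests for group comparisons, and also univariable and multivariable Cox regression for the primary outcome.

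Section 11.3.1 does not say which of these routes the interim takes.

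**The concern.** A failure in an implant patient is known on the day it happens. Freedom from failure is known only at about one year. At the interim nearly every event-free implant episode is therefore still pending, and a crude proportion has to do something with it. Leaving pending episodes out keeps the failures and removes the matching successes. Keeping them in the denominator as event-free ignores the failures still to come. Neither proportion estimates the 1-year outcome.

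Implant surgery is unlikely to be a small stratum: the protocol's German summary says that orthopaedic operations are mostly implant-related. At stake are the event rates put before the committee (the synopsis also plans congress presentation of part of the interim results) and the conditional power, which needs an information fraction and so depends directly on how pending episodes are counted.

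**Working it through.** **The plan's own figure.** Section 11.2: 10% vs 5% events, 80% power; section 11.3: two-sided 5%. Without continuity correction, n = [1.96·√(2·0.075·0.925) + 0.842·√(0.10·0.90 + 0.05·0.95)]² / 0.05² = 435 per arm after rounding up. With the correction, (n/4)·[1 + √(1 + 4/(0.05n))]² = 474. The stated 474 is reproduced, so 10% vs 5% are the planned rates used below.

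**Maturity at the interim.** For uniform enrolment over T months (assumption) and surgery on the day of inclusion (the most favourable case), the share of episodes with at least f months of follow-up is max(0, T − f)/T. It does not depend on the speed of accrual.

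| Interim at month | Full year (f = 12) | Window open (f = 10) | Past day 42 (f = 1.38) |
|---|---|---|---|
| 10 | 0% | 0% | 86% |
| 12 | 0% | 2/12 = 17% | 88% |
| 14 | 2/14 = 14% | 4/14 = 29% | 90% |

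A one-month lag from inclusion to surgery lowers the month-12 figures to 0%, 8% and 80%.

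**Event rates at month 12.** Assumptions not given in the protocol: 250 episodes per arm (half of 500), 50% implants, half of implant events by day 42 and the rest spread evenly to month 12, and a resolved implant success from month 10.

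- Implant events, control: 125 × 0.10 × [0.5·1.38/2 + 0.75·10.62]/12 = 8.7. Non-implant: 125 × 0.10 × (1 − 1.38/24) = 11.8. Total 20.4. Decolonization: half of that, 10.2.
- Resolved successes, control: implant 125 × (2/12) × (1 − 0.0953) = 18.8; non-implant 125 × (10.62/12) × 0.90 = 99.6. Decolonization: 19.8 and 105.1.
- Resolved episodes only: 20.4/138.8 = 14.7% vs 10.2/135.1 = 7.6%, z = 1.88.
- All included episodes: 20.4/250 = 8.2% vs 10.2/250 = 4.1%, z = 1.90.

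One count overstates the planned 10% vs 5% and the other understates it, but z is practically the same.

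**Information fraction t and conditional power.** Planned final totals: 1,000 episodes and 500·0.10 + 500·0.05 = 75 events. Under the current trend, CP = Φ[(z/√t − 1.96)/√(1 − t)]. At z = 1.0 (chosen for illustration):

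| Count | t | CP |
|---|---|---|
| Resolved episodes | (138.8 + 135.1)/1,000 = 27% | 48% |
| Events | 30.6/75 = 41% | 30% |
| Enrolled episodes | 500/1,000 = 50% | 22% |

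Setting CP = 30% and solving, z = √t·[1.96 − 0.524·√(1 − t)], gives futility limits of z ≈ 0.79, 0.99 and 1.12. The choice of count changes the decision only for an interim z between about 0.8 and 1.1.

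**Sensitivity to the implant share (assumed), same z = 1.0.** In the order resolved, events, enrolled: at 30% implants t = 34%, 43%, 50% and CP = 38%, 28%, 22%; at 70% implants t = 21%, 38%, 50% and CP = 61%, 33%, 22%. The counts fall on both sides of 30% in each case.

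**The case against.** The best defence is that 11.3.1 leaves the interim data set open and other parts of the protocol offer sound readings. Section 11.3 plans a univariable Cox model and analysis of the entire study population, and a crude comparison may simply mean an unadjusted one. An episode still in scheduled follow-up is not obviously missing under 11.4, which does not mention the interim. The outcome wording "at 6 weeks (and/or a 1 year for surgeries with implant" leaves room for day-42 status, which 86–90% of episodes would have reached. Data cuts and censoring rules often sit in a SAP or committee charter.

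Much of this stands. A reader might infer that the comparison necessarily counts implant failures and almost no implant successes. That is one possible reading, supported by 11.4 and the per-protocol definition, but the protocol does not state it.

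Two other inferences should be resisted. The first is that the timing makes a falsely significant efficacy result likely. The arithmetic does not support it: both arms shift together, and z is 1.88 or 1.90. The second is that this is the only review able to stop recruitment. Section 11.3.1 lets the committee call an additional interim, section 10.1.3 plans annual futility analyses, section 2.9 lets the sponsor-investigators terminate early, and section 1.6 places committee review "during the interim analyses (approximatively after one and two years into the study".

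The defence does not remove the point. The protocol itself fixes the calendar date, the crude comparison, the 30% limit and the dropout rule, and together these do not fit its 1-year implant outcome.

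**Conclusion.** The point holds as a timing conflict with consequences for the reported rates and for futility. The maturity shares follow from the protocol's own dates and uniform enrolment alone. The distortion of the rates (about 15% vs 8% or 8% vs 4%, against 10% vs 5%) and the spread of conditional power (48%, 30%, 22%) rest further on the assumed implant share, timing of implant events, 250 episodes per arm and interim z of 1.0. The sizes would change with other inputs. What remains is that an unstated counting choice can decide whether a result near the limit stops the trial. This should be corrected before the interim; it does not undermine the final analysis.

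**What to change.** In 11.3.1, state that:

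- the interim comparison and the conditional power use all randomized episodes as time to first primary event, in the univariable Cox model already planned in 11.3;
- event-free episodes are censored at the data cut, or at day 42 for non-implant surgery if that comes first;
- the information fraction is the number of observed events over the number planned;
- the dropout rule in 11.4 does not apply to episodes still in scheduled follow-up;
- day-42 status is reported for all episodes beside the main interim result.

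The cost is protocol wording and a little more interim programming, with no extra patients or visits. The interim date can stay as it is. The small downside is that the implant estimate at the interim will mainly reflect early events, which the interim report should say.

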| Publications                         | 
The study team at the Balgrist will present the at least part of the interim results in scientific congresses; and will publish the final results in one or two scientific surgical journals. The Protocol will be published separately, e.g. Journal "Trials".
                                                                                                                                                                                                                                                                                                                                                                                                                                                     |
| Donation                             | 
Schülke & Mayr GmbH will support the study with an unconditional donation of 55,000.- (fifty-five thousand) Swiss Francs (paid in two tranches), which will be used for the salary of the study / infection control nurses, the monitoring and for the Ethical Committee fees. The study team will not make financial profit and cover the minimal operational costs.
 
Schülke & Mayr GmbH will donate all the decolonization kits used for the study, for free (including the corresponding transport costs).
 
Schülke & Mayr GmbH has the rights to consult the data and the draft, but will not be part of the study / academic team that will publish the results of the BALGDEC study.
 |
|                                             |                                                                                                                                                                                                                                                                                                                                                                                                                                                                                                                                                                                                                                                                                                                            |

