#### *Periodic reporting of safety*

An annual safety report on the participant is submitted once a year to the local Ethics Committee via the Lead Investigator. We, moreover, will perform statistical interim (futility) analysis on an annual basis.

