### **11.2 Determination of Sample Size**

In our hospital, postoperative wound problems occur in at least 5% percent of all interventions. Incidence for both, revision surgery and/or SSI, in our selected patient population is set for 10% according to our clinical experience among the selected patient population that composes our study population.

We perform a superiority RCT with a power of 80% in favor of the decolonization. With 95% event-free surgeries in the decolonization arm versus 90% in the standard arm, we formally need 2 x 474 orthopedic surgery episodes, which we sum up to 2 x 500 surgeries (n = 1'000). A patient can be included several times as long as he/she gets not infected and has not witnessed postoperative wound problems.

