### 11.3 Planned Analyses

All analyses will be performed for the entire study population. In a second step, all analyses will be separately performed according to subgroups of patients, based on the type of orthopaedic surgical procedure (e.g. arthroplasties, implant-related surgeries, etc.). We will use descriptive statistics and will perform group comparisons (using the Pearson- $\chi^2$ -test, the Fischer-exact-test, or the Wilcoxon-ranksum-test), as appropriate. We will also perform composite (SSI and wound problems) and separate (SSI or wound problems) multivariate analysis using a Cox regression model targeting the co-primary outcome variables. For the primary outcome parameter, univariable and multivariable results will be computed using a Cox regression analysis. Variables with a  $p$  value  $\leq 0.2$  in univariate analysis will be included in a stepwise forward selection process for multivariate analysis. Key variables will be checked for co-linearity and interaction. The number of variables in the final model is limited to the ratio of 1 variable to 5 to 8 outcome events. The significance level is  $p \leq 0.05$  (two-tailed).

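### The interim stopping rule has no adjusted significance level and can be triggered by any objective; tested at 0.05 at one interim and again at the end, the primary outcome carries about 8% type I error, not 5%

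*Protocol*

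**What the plan says.** Section 11.3.1 plans one interim analysis at one year (± 2 months). The trigger for considering early termination is met "If group comparison between the decolonization and non-decolonization arms are striking and statistically significant in terms of any study objectives"; the independent committee then decides. The same section adds that "the Data Monitoring committee has the right to call on a premature, additional interim analysis". If the comparison is not conclusive, a futility check follows, using conditional power under the current trend with a 30% limit. Section 2.9 lists early evidence of benefit from interim analyses as a reason to end the trial.

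The level is fixed once, in section 11.3: "The significance level is" p ≤ 0.05, two-tailed. No interim boundary, spending function or reduced final level is given.

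Two other sections describe the looks differently. Section 1.6 has the committee at work "during the interim analyses (approximatively after one and two years into the study"). Section 10.1.3, under periodic safety reporting, says the team "will perform statistical interim (futility) analysis on an annual basis".

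On disclosure, the Synopsis (Publications) says the study team "will present the at least part of the interim results in scientific congresses", and section 13 foresees preliminary results at scientific meetings.

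**The concern.** A trial that tests at 0.05 at an interim, may stop there for benefit, and tests again at 0.05 at the end does not have a 5% type I error. The Protocol widens this in two ways. The trigger is not confined to the primary outcome, so a chance difference in adverse events or in a secondary revision outcome would satisfy it. The number of looks is open, because the committee may add some and three sections count the planned ones differently.

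At stake is whether a positive result can be reported at the two-sided 5% level the Protocol claims. A trial stopped on an unadjusted 0.05 at about half the data also tends to overstate the effect.

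Disclosure matters more here than usual. There is no blinding of patients and no placebo (section 6.2.2), and the treating physician's opinion settles doubtful wound outcomes (section 9.1). Knowledge of a between-arm interim result could therefore influence how later outcomes are judged.

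**Working it through.** **Inputs.** Two-sided 0.05 (section 11.3). Section 11.2: 80% power; "With 95% event-free surgeries in the decolonization arm versus 90% in the standard arm"; 474 per arm, raised to 500. Allocation 1:1 (section 6.2.1). Interim at 10 to 14 months (section 11.3.1). At least 600 eligible episodes a year, and 1,000 planned over two years (Synopsis).

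**1. The Protocol's own sample size.** With event rates 0.10 and 0.05 (mean 0.075):

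n = [1.960·√(2·0.075·0.925) + 0.842·√(0.10·0.90 + 0.05·0.95)]² / 0.05² = 434.4, so 435 per arm.

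With continuity correction: n′ = (n/4)·[1 + √(1 + 4/(n·0.05))]² = 473.6, so 474.

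This matches the stated figure exactly. It shows that the full two-sided 0.05 was given to a single final test.

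**2. Information at the interim.** Accrual of 500 to 600 episodes a year gives 500·10/12 = 417 at the earliest and 600·14/12 = 700 at the latest, out of 1,000. The fraction t is therefore about 0.4 to 0.7. Implant cases need one year of follow-up, so the fraction with complete outcomes may be lower.

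**3. Type I error on the primary outcome, one interim plus final, each at |Z| ≥ 1.96.** The two statistics are bivariate normal with correlation √t, and the error is 1 − P(|Z₁| < 1.96 and |Z₂| < 1.96).

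| t | Type I error |
|---|---|
| 0.4 | 8.6% |
| 0.5 | 8.3% |
| 0.6 | 8.0% |
| 0.7 | 7.6% |

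Simulated Pearson chi-square tests on binary data agree: 8.2% for 250 then 500 per arm, 8.0% for 300 then 500.

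**4. One extra efficacy look at 0.05.** The Protocol gives no timing, so these are illustrations: 9.8% for looks at 0.5/0.75/1, 11.0% for 0.3/0.6/1, 11.4% for 0.25/0.5/1.

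**5. Futility rule treated as binding (one interim, t from 0.4 to 0.6).** 7.3% to 6.9% if conditional power follows the trend in either direction; 6.2% to 5.9% if it counts benefit only.

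**6. Upper scenario for the any-objective trigger.** Three objectives can be compared between arms: the primary composite, non-infection revision surgery and adverse events. The questionnaire is confined to decolonized patients. Assume that significance on any of the three stops the trial automatically at t = 0.5, and that otherwise the primary is tested at 0.05 at the end. The chance of a false stop or a false final primary result is:

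| Correlation between objectives | Probability |
|---|---|
| 0 | 17.2% |
| 0.3 | 16.6% |
| 0.5 | 15.5% |
| 0.7 | 13.8% |

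With two objectives it is 12.9% (correlation 0) to 11.4% (correlation 0.7).

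**7. A boundary that holds 5%.** Lan-DeMets O'Brien-Fleming-type spending, 0.025 per side: cumulative two-sided alpha at t is 4·[1 − Φ(2.2414/√t)].

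- t = 0.5: 4·[1 − Φ(3.170)] = 0.0031, |Z| ≥ 2.963; final p ≤ 0.0490.
- t = 0.6: 0.0076; final p ≤ 0.0476.

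For a design with 80.0% power at a single test, power becomes 79.9% at t = 0.5 and 79.7% at t = 0.6.

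**The case against.** **The rule is not a bare p ≤ 0.05.** Section 11.3.1 asks for a striking as well as a significant difference, leaves the decision to an independent committee, and states no p-value in that sentence. This stands as a limit on the figures: they assume that 0.05 applies at the interim, because no other level exists, and that crossing it stops the trial. A cautious committee would produce fewer false stops. But neither safeguard has a number, so neither guarantees 5%.

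**Boundaries often sit in a SAP or committee charter.** That is true of the numerical boundary. Here, however, the Protocol itself fixes the trigger, the right to extra looks and the single 0.05 level, and a later document would have to contradict it.

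**Stronger readings that a reader might infer, and that the text does not support:**

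- That the false-positive rate is 8–17%. The upper figure is the chance of a false stop on any of three independent objectives or a false final primary result, which is a different quantity from primary type I error. Independence is also doubtful: the primary composite includes revisions for non-infected wound problems, which overlaps the secondary outcome of non-infection revisions. The number of objectives is itself unsettled, since section 4 names fewer than section 9.1.2.
- That every annual look spends alpha. Section 10.1.3 labels those looks futility, and a futility-only look does not raise type I error. The second look in section 1.6, at about two years, falls at the end of the 24-month interventional part.
- That comparative results will be shown while patients are still being enrolled. The Synopsis says only that part of the interim results will be presented; it does not say by arm or when. This is a risk to close off, not a stated plan.

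**Conclusion.** Wrong as written. The Protocol permits early stopping on an unadjusted, any-objective significance criterion and allows further looks, while claiming a two-sided 5% level that its sample size spends entirely on the final test.

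If 0.05 is applied at one interim and at the end, primary type I error is about 8%. That rests on an information fraction of 0.4 to 0.7, non-binding futility and stopping whenever 0.05 is crossed. Binding futility brings it to about 6–7%, still above 5%; one extra efficacy look takes it to roughly 10–11%. The 14–17% for a false stop or false final result across three objectives is an upper scenario only.

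Separately, the Protocol gives three accounts of the looks: one (11.3.1), after one and two years (1.6), and annual for futility (10.1.3). These need reconciling whatever boundary is chosen.

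**What to change.** - **Section 11.3.1, trigger.** Restrict the efficacy stopping rule to the primary composite and delete the reference to any objective from it. Leave the committee's discretion to stop for harm untouched.
- **Sections 11.3 and 11.3.1, level.** State a Lan-DeMets O'Brien-Fleming-type spending function at overall two-sided 0.05, applied at the actual information fraction. At 0.5 this gives |Z| ≥ 2.963 (p ≤ 0.0031) and final p ≤ 0.0490; at 0.6, p ≤ 0.0076 and final p ≤ 0.0476. Any additional efficacy look draws on the same function. Interim and final levels must be used as a matched pair: at half information a looser interim boundary of |Z| ≥ 2.77 needs a final level of 0.0478, and combining it with 0.0490 would give 5.12% overall.
- **Sections 1.6, 10.1.3 and 11.3.1, number of looks.** Give one schedule and say which looks are for futility only.
- **Synopsis (Publications) and section 13.** State that no between-arm interim results are released before final database lock.

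The cost is a wording amendment, a power loss below 1 percentage point, a harder threshold for stopping early for benefit, and no between-arm interim results at congresses.

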| Number of Participants with Rationale                                 | Postoperative wound problems occur in at least 5% percent of all interventions. Incidence for both, revision surgery and/or SSI, in our selected patient population is set for 10%. We perform a superiority RCT with a power of 80% in favor of the decolonization. With event-free surgeries to 95% in the decolonization arm versus 90% in the standard arm, we formally need 2 x 474 surgery episodes, which we sum up to 2 x 500 surgeries (n = 1'000). A patient can be included several times as long as he/she gets not infected.

At the Balgrist, we perform at least 5000 surgical operations per year (in reality more than 6000). With a very conservative estimation, we see at least 600 surgical episodes per year (12% of surgeries) that can be included; mostly because of the advanced age, diabetes, and high ASA-Scores of our patients. The interventional part of the trial lasts two years; with interim analysis after 1 year (+/- 2 months). An independent advisory board might stop the trial. For the secondary outcomes (adverse events, questionnaire), we do not require a minimal sample size. |                            |                            |          |          |             |          |          |          |                              |              |                            |                            |                     |       |       |   |               |       |       |       |                          |        |        |        |                      |       |       |       |                  |       |     |       |                           |               |               |               |

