## 4. STUDY OBJECTIVES

To reduce the incidence of SSI (and other unplanned postoperative wound revisions) in a highly selected patient population with an elevated risk for SSI. To show the safety and all potential (any) adverse events observed during the decolonization period and during the hospitalization for surgery.

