### Secondary outcomes:

- Unplanned revision surgery for non-infection problems in same time period
- All adverse events during decolonization and hospitalization for surgery
- Subjective opinion on the decolonization (only for patients being decolonized)

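### The interim rule in section 11.3.1 makes the committee's stopping decision conditional on statistical significance for harm as well as efficacy, which conflicts with section 2.9

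*Protocol*

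**What the plan says.** **The interim rule.** Protocol section 11.3.1 plans one interim analysis about a year after the first inclusion. When the comparison of the two groups looks "striking and statistically significant in terms of any study objectives, the independent Data Monitoring committee will decide upon the interruption"; the same decision covers ending the study early. The next sentence is "Otherwise, the study continues". The committee may also ask for an additional, earlier interim analysis. If the crude comparison is not informative enough, a futility calculation follows.

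**What counts as an objective.** Section 4 gives two objectives. The first is to reduce infections and wound revisions. The second is "To show the safety and all potential (any) adverse events observed during the decolonization period and during the hospitalization for surgery". The matching secondary outcome in section 5 is "All adverse events during decolonization and hospitalization for surgery". The phrase about any study objective in 11.3.1 therefore covers adverse events.

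**The test and its size.** Section 11.3 names descriptive statistics and group comparisons (chi-square, Fisher, rank-sum) with a two-tailed level of 0.05. On numbers, the synopsis (Number of Participants with Rationale) says: "For the secondary outcomes (adverse events, questionnaire), we do not require a minimal sample size".

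**Other routes to stopping.** Section 2.9 allows the sponsor-investigators to end the study when participants' safety is in doubt, or on early evidence of benefit or harm, for example from interim analyses. It sets no significance condition. Section 1.6 has two persons independent of the investigators monitor safety at the interim analyses. The synopsis says that an independent advisory board might stop the trial, again without a condition.

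**The concern.** A significance condition is a usual safeguard for efficacy, because it protects against stopping on a chance benefit. Section 11.3.1 applies the same condition to every objective, so it also governs harm, where the considerations are different. A safety committee normally acts on the pattern, seriousness and plausibility of events, often with too few of them for a formal test.

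Taken literally, the text also gives the independent committee a higher threshold for harm than the sponsor-investigators have under 2.9. Yet the committee is the body charged in 1.6 with watching safety at that look. Section 3.6 itself foresees more skin irritation, intolerance and allergy in the decolonization arm, so an imbalance is a realistic case. If one occurred, the committee would have one section telling it that the study goes on and another treating the same data as grounds to stop.

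**Working it through.** **1. The passages side by side**

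| Place | Who decides | Condition for stopping on safety |
|---|---|---|
| 11.3.1 | Independent committee | Difference striking and statistically significant on any objective; otherwise continue |
| 2.9 | Sponsor-investigators | Safety in doubt, or early evidence of harm; no test |
| 1.6 | Independent committee | Monitors safety at the interim; no threshold |
| Synopsis, Number of Participants | Independent advisory board | Might stop the trial; no condition |

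The first row is stricter than the others, and no cross-reference says which governs. The additional interim analysis allowed in 11.3.1 gives another look but states no different threshold.

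**2. The plan's own sample size**

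Inputs from 11.2 and 11.3: 10% versus 5%, power 80%, two-sided 0.05.

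- Uncorrected: n₀ = [1.96·√(2·0.075·0.925) + 0.8416·√(0.10·0.90 + 0.05·0.95)]² / 0.05² = 434.4, so 435 per arm.
- With continuity correction: n = (n₀/4)·[1 + √(1 + 4/(n₀·0.05))]² = 473.6, so 474 per arm.

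This matches the stated 474, raised to 500. It applies to the primary outcome only. There is no corresponding figure for adverse events.

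**3. Size of the interim look**

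Half of the planned 1,000 episodes gives 250 per arm. The synopsis estimate of 600 eligible episodes per year gives 300 per arm if all are enrolled.

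**4. Chance that a true harm is not significant**

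The protocol gives no adverse-event rates, so the rates below are assumptions, with the higher rate in the decolonization arm. The calculation takes one comparison, independent episodes and two-sided 0.05.

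Miss probability ≈ 1 − Φ[(δ − 1.96·SE₀)/SE₁], where SE₀ = √(2p̄(1−p̄)/n) and SE₁ = √([p₁(1−p₁) + p₂(1−p₂)]/n).

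Example, 2% versus 4% with n = 250:

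- 1.96·SE₀ = 1.96·√(2·0.03·0.97/250) = 0.0299
- SE₁ = √((0.0196 + 0.0384)/250) = 0.0152
- (0.02 − 0.0299)/0.0152 = −0.65, so the miss probability is 1 − Φ(−0.65) = 0.742

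Exact enumeration of the two binomials with the Pearson chi-square gives 0.741. Exact results for all cases:

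| Assumed rates | 250 per arm | 300 per arm | 500 per arm (final) |
|---|---|---|---|
| 1% vs 2% | 87% | 84% | 76% |
| 2% vs 4% | 74% | 70% | 54% |
| 5% vs 7.5% | 79% | 75% | 63% |
| 10% vs 15% | 61% | 54% | 33% |
| 5% vs 10% | 43% | 35% | 14% |

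Fisher's test, which 11.3 also allows, is less sensitive at low rates. For 2% versus 4% at 250 per arm its power is 17.8%, a miss probability of 82%.

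**5. One concrete interim table**

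Take 5/250 in controls and 10/250 with the set, a doubling. The difference is 0.02, the pooled rate 0.03 and the SE √(2·0.03·0.97/250) = 0.01526. So z = 1.31 and p = 0.19. Under the literal wording of 11.3.1 the study continues, whatever the committee makes of the ten events.

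**The case against.** The best reply is that stopping for safety does not depend on 11.3.1. Section 2.9 allows it without a test, 1.6 sets up independent safety monitoring, and the synopsis lets an advisory board stop the trial. Sections 10.1.2 and 10.1.3 add causality and severity assessment of individual events, 24-hour SAE reporting, SUSAR and safety-signal reporting and annual reports. None of these needs a p-value. Within 11.3.1 the committee may call an extra look, and the futility step shows that the sentence on continuing is not absolute. The miss probabilities also rest on rates that the protocol does not supply.

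Most of this stands. Harm would not go unseen, and a sensible committee would probably act. But the section 10 provisions are mainly about single events and reporting. They do not say when the committee may act on an imbalance between arms. The one passage that does is 11.3.1, and it ties the decision to significance.

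Three stronger readings are tempting, and the document supports none of them:

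- A reader might infer that a non-significant adverse-event difference will be taken as proof of safety. The protocol never says so. The second objective can be read as presenting the events observed, and setting no minimum sample size for them fits a descriptive aim.
- A reader might infer that the difference test is the only tool for adverse events. Section 11.3 also names descriptive statistics.
- A reader might infer that harms are missed most of the time at the final analysis. At 500 per arm this depends on the assumed rates: 54% for 2% versus 4%, but 33% for 10% versus 15% and 14% for 5% versus 10%.

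**Conclusion.** The point holds as a contradiction in the stopping provisions. Section 11.3.1 applies an efficacy-type significance condition to safety, and this conflicts with 2.9, with the committee's role in 1.6 and with the unconditional stopping sentence in the synopsis.

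Its practical size can only be shown for assumed rates. With 250 to 300 episodes per arm, a two-sided 0.05 chi-square test fails to flag 2% versus 4% about 70–74% of the time, 10% versus 15% about 54–61%, and 5% versus 10% about 35–43%. These figures assume independent episodes and a single comparison. Testing several event types would raise the chance that something reaches significance. The further requirement that a difference be striking, which is not defined, would lower it.

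The conclusion concerns the interim rule only. Confidence intervals by event class, safety margins and upper-limit statements commonly belong in a statistical analysis plan, which is not at hand, and their absence is not a finding.

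**What to change.** In section 11.3.1, restrict the condition of a striking and statistically significant difference, and the sentence on continuing, to the primary efficacy outcome. Add that at each interim look the committee reviews adverse events and SAEs by arm and may recommend termination for safety without a significance requirement. Cross-refer this to 2.9, and make 1.6 and the synopsis sentence on the advisory board consistent with it.

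The cost is a sentence or two of protocol text. No extra patients, visits or data are needed, since adverse events are already recorded. The downside is that the decision on harm rests on the committee's judgement rather than on a p-value, so its reasons for recommending that the trial stop or continue should be minuted.
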